### Cost analysis

Cost will be calculated from healthcare and societal perspectives during the 12 months before the screening and during the 12 months before the last follow-up. The cost of pharmacological therapy, medical tests, and use of health services will be added together to calculate direct healthcare costs. Indirect costs such as loss of productivity will be calculated considering the minimum daily wage in Spain and the number of sickness absence days. Total costs will be estimated by adding up direct and indirect costs in €. The effectiveness of the interventions will be estimated as the difference between the BDI-II score at baseline and at follow-up, and utility will be estimated using quality-adjusted life-year (QALYs) at follow-up. QALYs will be calculated using the area-under-the-curve (AUC). Cost-effectiveness will be analyzed through the estimation of incremental cost-effectiveness ratios (ICERs). Cost-utility will be calculated through the estimation of incremental cost-utility ratios (ICURs). Cost-utility planes will be plotted.

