**Methods:**

A randomized controlled clinical trial will be conducted in PC, with about 120 depressed patients allocated (1:1:1) to three groups: “face-to-face MBI + TAU”, “Internet-delivered MBI + TAU”, and “TAU alone”. The MBI programs will be composed of four modules. The primary outcome will be depressive symptoms, measured through the Beck Depression Inventory, assessed at pre- and post-treatment and 6- and 12-month follow-ups. Other outcomes will be mindfulness, happiness, affectivity, quality of life, and the use of healthcare services. Intention-to-treat analysis using linear mixed models adjusted for baseline scores and routine sociodemographic analysis that could show baseline differences will be conducted. Per-protocol secondary outcome analyses will also be performed.

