### Randomization and blinding

Participants who meet the inclusion criteria for the study will receive a code from the screening assessors in order to maintain participants’ confidentiality. An independent researcher unaware of the study characteristics will perform the randomization process. In order to randomly allocate the participants to one of the three conditions referred to above (face-to-face MBI + TAU, Internet delivered MBI + TAU, and TAU alone), a computer-generated random number sequence (https://www.randomizer.org/) will be used by means of a simple allocation strategy and a 1:1:1 rate. After informing the patients of the study characteristics, they will accept to participate before the random allocation and without knowing the condition to which they will be allocated. The researcher who administers baseline assessments will be blind to the patients’ treatment group. This researcher will be different from the one – also blinded – who administers the other measures throughout the study. Patients in the Internet-delivered MBI arm will complete all the measures online. GPs will be blind, but the face-to-face MBI therapist will not. Participants will not be blind to the treatment condition for ethical and practical reasons.

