### Sample size

The sample size estimation was based on testing whether the trend in the change is different between the intervention groups throughout the 4 time points. Firstly, we assumed that MBI groups would be able to present moderately high effects, compared to “TAU alone”, on the BDI-II at post-treatment. To operationalize this, we considered a standardized difference between arms on the main outcome of d = 0.7, which corresponds to the average effect observed in ten studies comparing MBIs with different wait-list conditions [36] and surpasses the 0.5 standard deviation criterion considered clinically relevant in previous studies [37, 38]. A preceding study by our research group with mild or moderate depressed patients in a similar Spanish PC setting found BDI-II means and standard deviations (SDs) of 22 and 5, respectively [20]. The inclusion criteria used in this study restricted the entry of mild or moderate depressed patients, thus reducing the SD compared to the general population and presenting a less skewed distribution of the data, as we predict will occur in the present study. The effect size referred to above corresponds to a difference of 3.5 points, which implies a reduction of slightly more than 15% in the BDI-II scale used. According to the GLIMMPSE v2.0.0 – time x group interaction in a general linear repeated measures (RM) design – and GPower v3.1.9.4 – ANOVA test for RM within-between interaction – statistical tools, considering the referred difference between the “face-to-face MBI + TAU” vs. “TAU alone” groups of depressed patients, which corresponds to a partial eta square value of roughly 0.09 and an effect size f of 0.31, with a common mean at baseline of 22, a mean at post-test of 16 and 19.5 respectively, and a mean at post-test of 17 for the “Internet delivered MBI + TAU” condition, and assuming a one point reduction in each group at each following time point, a baseline correlation of 0.6 and a decay rate of 0.35, assuming a common SD of 5, a 5% significance level, a statistical power of 80% using a 1:1:1 ratio, and an univariate approach to RM with Greenhouse-Geisser correction [39], we needed 33 subjects in each group. Because we expected a dropout rate of approximately 20% [40], we inflated the numbers to reach a total sample size of 120 patients, 40 per arm [41].

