### Instruments

The evaluations will be performed at screening, baseline, post-treatment, and 6- and 12-month follow-ups. All variables and assessment periods of the study can be found in Table 1. Scores on depression, negative and positive affect, and opinions about the modules will also be obtained after each completed module in the face-to-face and Interned-based MBIs. Participants in the TAU group will report their general opinion about the treatment as usual received at the end of the program.

**Table 1 Tab1:** Study outcomes

Instruments	Assessment Area	Time of assessment^a^
Sociodemographic	Gender, age, marital status, education, occupation, economical level.	Screening
MINI	Psychiatric diagnosis	Screening
PHQ-9	Severity of depression	Screening, post-module, post-treatment and follow-ups
CSRI	Health and social services use	Screening and 12-month follow-up
BDI-II	Severity of depression	Baseline, post-treatment and follow-ups
SF-12	Health-related quality of life	Baseline, post-treatment and follow-ups
EQ-5D	Health-related quality of life	Baseline and follow-ups
PANAS	Positive and negative Affect	Baseline, post-modules and follow-ups
FFMQ	Facets and factors of mindfulness	Baseline and follow-ups
PHI	Remembered and experienced well-being	Baseline and follow-ups
ETS	Treatment expectations	Baseline
OTS	Treatment opinions	Post-treatment

*MINI* Mini-International Neuropsychiatric Interview, *PHQ-9* Patient Health Questionnaire-9, *CSRI* Client Service Receipt Inventory, *BDI-II* Beck Depression Inventory-II, *SF-12* Short Form-12 Health Survey, *EQ-5D* EuroQoL-5D Questionnaire, *PANAS* Positive and Negative Affect Scale, *FFMQ* Five Facet Mindfulness Questionnaire, *PHI* Pemberton Happiness Index, *ETS* Expectation of Treatment Scale, *OTS* Opinion of Treatment Scale.

^a^Waves: screening, baseline, post-treatment (6 weeks for the “face-to-face MBI + TAU” and “TAU alone” or 12 weeks after baseline for the “Internet-delivered MBI + TAU”), post-module (after each individual module for the “face-to-face MBI + TAU” and for the “Internet-delivered MBI + TAU”), follow-ups (both 6 and 12 month follow-up measurements)

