### Main analysis

The efficacy of the “face-to-face MBI + TAU” group compared to the “TAU alone” group will be estimated based on the main BDI-II outcome, which will be considered a continuous variable. Multilevel mixed-effects models will be developed by means of a RM design on an intention-to-treat (ITT) basis, using the restricted maximum likelihood (REML) method, in order to produce unbiased estimates of variance/covariance parameters [54]. Non-standardized slopes and 95% confidence intervals (95% CI) will be calculated by adjusting those variables that show significant differences between groups at baseline. In order to study the specific trajectories of each group throughout the trial and determine whether possible differences between groups are consistent over time, the ‘group x time’ interactions will be calculated. Cohen’s d effect sizes will be calculated at each time point using the combined standard deviation at baseline [64]. Effect sizes are small when d ≤ 0.2; medium when d = 0.5; and large when d ≥ 0.8 [65].

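### The economic analysis takes its BDI-II effect as a raw change score with no baseline adjustment named; adjusting for baseline BDI-II and baseline EQ-5D would be a small, free gain in precision

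*Protocol article*

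**What the plan says.** The Cost analysis section fixes the effect measure for the ICER: "The effectiveness of the interventions will be estimated as the difference between the BDI-II score at baseline and at follow-up". For the ICUR it says that "QALYs will be calculated using the area-under-the-curve (AUC". It names no regression model and no covariate for either between-arm difference.

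Both baselines are collected. Table 1 (Instruments) lists BDI-II at baseline, post-treatment and both follow-ups. It lists EQ-5D at "Baseline and follow-ups", where follow-ups means 6 and 12 months.

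Baseline adjustment is mentioned only for the clinical analysis, and in two forms. The abstract announces "Intention-to-treat analysis using linear mixed models adjusted for baseline scores". The Main analysis section speaks only of "adjusting those variables that show significant differences between groups at baseline". Neither is tied to the cost analysis.

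Patients are allocated "by means of a simple allocation strategy and a 1:1:1 rate", and no stratification is named. The Sample size section assumes "a baseline correlation of 0.6 and a decay rate of 0.35", a common SD of 5 and 40 patients per arm.

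**The concern.** A change score subtracts the whole baseline value, although follow-up depends on it only in part. When the correlation between the two is well below 1, this over-corrects. An arm that happens to start with higher BDI-II scores will tend to show a larger fall, with or without a treatment effect. Simple randomization with 40 per arm leaves room for such gaps.

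The ICER divides by this effect, so noise in the denominator feeds into the ratio. The article makes cost-effectiveness a stated hypothesis in the Background, so the estimator deserves some care.

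QALYs have a related feature. Baseline utility is itself part of the area, so a baseline gap enters the QALY total directly unless the arm comparison adjusts for it.

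**Working it through.** **Inputs.** From Sample size: SD 5, correlation 0.6 with decay 0.35, planned difference 3.5 points, 33 per arm before and 40 after inflation for dropout. From Level of significance: two-sided 0.05. The plan gives no utility SD, correlation or expected QALY effect, so the utility correlations in step 4 are assumptions.

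**1. The plan's own figure.** "The effect size referred to above corresponds to a difference of 3.5 points", that is 0.7 × 5. A two-sided 5% comparison of two means with 80% power gives 33 per arm (exact power at 33: 0.800), and 33 × 1.2 = 39.6, so 40 per arm and 120 in total. Both figures reproduce. A three-arm group-by-time test with the stated means and a linear-exponent correlation gives power of 0.81 to 0.82 at 33 per arm, so that reading of the correlation fits the plan.

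**2. BDI-II precision at 12 months.** The correlation is r = 0.6^1.35 = 0.502.

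- Change score: variance 2(1 − r) = 0.996 SD².
- Baseline-adjusted: variance 1 − r² = 0.748 SD².
- Ratio: 0.996 / 0.748 = 1.33.
- Standard error of the arm difference at 40 per arm: 5 × √0.996 × √(2/40) = 1.12 against 5 × √0.748 × √(2/40) = 0.97 points.

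At r = 0.50 the change score has the same variance, about 1.00 SD², as the follow-up score alone. At 6 months (r about 0.55) the adjusted variance is 0.77 of the change-score variance. In general this ratio is (1 + r)/2, so it runs from 0.65 to 0.90 for r from 0.3 to 0.8.

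**3. Carry-over of a chance baseline gap.** The standard error of the baseline difference is 5 × √(2/40) = 1.12 points, with a 95% range of ±2.19. The change score carries 1 − r = 0.498 of the gap, so a typical carry-over is 0.498 × 1.12 = 0.56 points and the 95% limit is 0.498 × 2.19 = 1.09. The planned difference at 12 months is still 3.5 (14 against 17.5, after one point off each arm at each later wave), so the 95% limit is 1.09 / 3.5 = 31% of it. A simulation of 10,000 trials gave a carry-over of 0.497 in size for the change score and about 0 for the adjusted estimate.

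With 33 per arm analysed, the standard errors are 1.23 and 1.06, and the 95% limit of the carry-over is 1.20.

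**4. QALYs, if the arms were compared without adjustment.** Linear interpolation over 0, 6 and 12 months gives weights of 0.25, 0.50 and 0.25. Equal variances at each wave are assumed.

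| Assumed utility correlation | Carry-over per unit of baseline gap | Adjusted / unadjusted variance |
|---|---|---|
| 0.3, falling to 0.3^1.35 = 0.197 over 12 months | 0.25 + 0.5(0.3) + 0.25(0.197) = 0.45 | 0.348 / 0.550 = 0.63 |
| 0.3 throughout | 0.25 + 0.75(0.3) = 0.475 | 0.337 / 0.562 = 0.60 |
| 0.8 throughout | 0.25 + 0.75(0.8) = 0.85 | 0.152 / 0.875 = 0.17 |

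**The case against.** The best reply is that the Cost analysis section defines an outcome, not a between-arm model. Regressing BDI-II change on arm and baseline gives exactly the same arm coefficient as regressing follow-up on arm and baseline. A change-score outcome therefore does not rule out adjustment, and the 33% penalty applies only if mean changes are compared directly. That condition stands. But the sentence says that effectiveness will be estimated as the change and adds nothing, so the direct comparison is its natural reading.

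Four stronger readings are tempting, and the documents do not support them.

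- **That the plan states an unadjusted QALY comparison.** The area-under-the-curve sentence tells us how each patient's QALYs are computed. It is silent on how arms are compared, and a condensed article may leave that to the full plan.
- **That prior cost differences pass into incremental cost and call for a prior-cost covariate.** No cost model is stated. The service-use inventory is described as covering 6 months, while Cost analysis counts 12 months before screening, so a 12-month prior-cost covariate is not shown to be collected.
- **That clinical and economic analyses must give different BDI-II effects.** This rests on the abstract alone. The Main analysis section adjusts only for variables that differ significantly at baseline and fits a group-by-time model. If baseline is one of the waves and data are complete, that contrast at 12 months equals the difference in mean change.
- **That the imbalance can be as large as the effect.** No expected QALY or cost effect is given to compare with. For BDI-II, the 95% limit is about 1.1 points against 3.5.

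Nor is this systematic bias. Imbalance under randomization averages out over repeated trials.

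**Conclusion.** The point holds as a minor one. For the BDI-II increment, the plan states a change score and names no adjustment. On its own correlation, comparing arms on that change costs about a third in variance and leaves a conditional error of about half of any chance baseline gap. This rests on the linear-exponent reading of the correlation, a common SD of 5, 40 analysed per arm, and a direct comparison of mean changes.

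For QALYs the point is weaker: the adjustment is neither stated nor excluded, and the size depends on assumed utility correlations. It is worth settling in the same sentence, because baseline utility has a direct weight of 0.25 in the area.

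The primary analysis and the sample size are unaffected.

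**What to change.** Add to the Cost analysis section that:

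- the incremental BDI-II effect is the arm coefficient from a regression of follow-up BDI-II on arm and baseline BDI-II, or the corresponding contrast from a mixed model with baseline BDI-II as a covariate;
- incremental QALYs are the arm coefficient from a regression of the area-under-the-curve QALYs on arm and baseline EQ-5D index;
- these adjusted increments are the denominators of the ICER and the ICUR.

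The present definition of effectiveness as change may stay if baseline BDI-II is added as a covariate, since the arm coefficient is then identical. If the mixed model is used, baseline should not be just another wave with a free mean in each arm, because that returns the difference in mean change.

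The cost is a few lines of text. Both covariates are already collected at baseline, and neither data collection nor sample size changes.

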### Level of significance

An alpha level of 0.05 will be established using a two-tailed test. The probability values relative to the main analysis will be adjusted according to Benjamini-Hochberg’s correction for multiple comparisons, but the secondary and exploratory analyses will not be corrected.

## Discussion

Consistent with the evidence, a large percentage of patients seen in PC services are being treated long-term with antidepressants, showing high relapse rates when trying to stop the medication [67], and many of them are referred to already overloaded specialized mental health services [68]. Therefore, there is a need to offer new forms of treatment that provide stability or improvement before moving on to specialized care. Currently, a growing number of studies show the efficacy of MBIs for emotional disorders, but only a few have focused on PC settings [69]. In this context, the present study protocol describes a randomized controlled clinical trial that has the main objective of evaluating a low-intensity MBI plus TAU for the treatment of depression in PC services compared to TAU alone.

Additionally, the advantages of brief Internet-delivered psychotherapy for depression could provide an alternative to current treatments and a possible solution for existing problems, especially with regard to waiting lists, lack of time, and health costs of PC Spanish services. Moreover, the effectiveness of Internet-based treatments for this disorder has also been demonstrated, and this kind of protocol can help to spread evidence-based treatments, so that more people can benefit from them [21, 70]. Specifically, mindfulness has been proposed as a potential non-drug therapy for mild-to-moderate depression [71] and for preventing depression relapses [72]. The study of mindfulness-based online interventions is increasing due to their good results and the benefits that have begun to be observed [27, 31].

The study has various strengths. First, to the best of our knowledge, this is the first Spanish randomized controlled clinical trial to apply a face-to-face brief MBI, and the second study to apply an online low-intensity MBI in PC settings [10]. Second, this study proposes two different ways to apply mindfulness treatments, which will allow us to compare them with TAU and find out which one is more cost-effective. Lastly, this will be the first study to compare a traditional face-to-face vs. online mindfulness program in the Spanish PC context, although in an exploratory way.

The limitations are similar to those of the study carried out by Castro et al. [10], who refer to possible negative attitudes from GPs about recommending this treatment, and high dropout rates in the treatment groups, especially in the control group. To minimize the effect of negative attitudes, the intervention characteristics will be explained in depth to the clinicians involved in the trial. In order to prevent dropouts, we will send emails to the participants reminding them to continue and complete the trial requirements. Another limitation is the possible small statistical power to obtain significant results in the comparison of the face-to-face and online MBI groups, but, as mentioned above, this study will be considered a pilot exploration of possible effect sizes to guide future research. Other difficulties that may appear could be related to recruitment because some people might not have access to the Internet at home, or they might even prefer traditional treatments (due to unawareness of the benefits of the new treatments and technologies) or be influenced by the depressive symptoms themselves (apathy, anhedonia, etc.).

### Clinical implications

Positive results of this randomized controlled clinical trial may have an important impact on public PC and mental health settings because applying a brief psychotherapeutic protocol to treat mild or moderate depression could help to decrease the overload of the public mental health system. On the one hand, it could reduce costs, waiting lists, hours of clinical assistance, and hours of face-to-face treatment. On the other hand, it offers treatment alternatives beyond antidepressant medication that can help to reduce depressive symptoms and slow down the inclusion of patients in mental health services by offering high-quality and flexible interventions in PC [73].

Finally, benefits of mindfulness in different disorders and in quality of life outcomes have been reported by several studies [74, 75]. Thus, although this study focuses mainly on depression, this proposal could also be used as a trans-diagnostic protocol in other comorbid psychological problems or emotional disorders (e.g. anxiety disorders) [71]. However, this is a brief treatment protocol, and research should be carried out in this regard. In conclusion, significant results from this trial could be beneficial for society and public health as a whole and encourage further research along these lines.

## Data Availability

Not applicable.

## Abbreviations

AUC: Area-under-the-curve
BDI-II: Beck depression inventory II
CBT: Cognitive behavioral therapy
CI: Confidence intervals
CSRI: Client service receipt inventory
EQ-5D: EuroQoL-5D
ETS: Expectation of treatment scale
FFMQ: Five facet mindfulness questionnaire
GP: General practitioner
ICERs: Cost-effectiveness ratios
ICURs: Cost-utility ratios
ITT: Intention to treat
MBCT: Mindfulness-based cognitive therapy
MINI: Mini international neuropsychiatric interview V-5.0.0
OTS: Opinion of treatment scale
PANAS: Positive and negative affect scale
PC: Primary care
PHI: Pemberton happiness index
PHQ: Patient health questionnaire
QALYs: Quality-adjusted life-year
REML: Maximum likelihood
RM: Repeated measures
SF-12: Sort Form-12 health survey
TAU: Treatment as usual
WHO: World health organization
